#### **STATISTICAL ANALYSES**

- Phase I trial (Dose escalation part)
  - All analyses will be descriptive; no p-values will be calculated.
  - Primary endpoint will be analyzed on the population assessable for safety of the phase I trial (escalation part).
  - Toxicity observed at each dose level, graded according to the Common Terminology Criteria for Adverse Events v5.0 from the NCI, will be recorded in terms of event type, severity, dates of beginning and end, reversibility and evolution. Data will be gathered in tables summarizing toxicities and side effects for each dose level and cycle.
  - DLT will be described in terms of number and incidence rates at each dose level. The number and percentage of patients who will have developed a DLT in each dose level will also be reported.
  - Data analyses will be provided by dose groups and for all study patients, combined wherever appropriate.
  - Categorical endpoints: best overall response, ORR under treatment and at 6 months, 6-month ORR and 6-month PFR, will be reported in terms of counts by dose level.
  - Continuous endpoints, e.g. GMI, will be reported in terms of summary statistics that will include number of patients, median, minimum, and maximum, and additional percentiles if appropriate.
  - Survival endpoints (PFS and OS) will be analyzed using the Kaplan-Meier method. The median survival rates will be reported with a 95% confidence interval. Median follow-up will be calculated using the reverse Kaplan-Meier method.
  - Missing data will not be imputed.
- Phase II trials
  - All analyses will be descriptive; no p-values will be calculated.
  - Analyses will be conducted independently for each phase II trial.
  - Analysis of the primary efficacy endpoint will be analysed based on the eligible population assessable for efficacy.
  - Same statistical methods as for the phase I trial.

| Schedule of assessments and procedures                  |               |                             |                 |     |                  |                             |                 |     |                  |                 |                |                            |
|---------------------------------------------------------|---------------|-----------------------------|-----------------|-----|------------------|-----------------------------|-----------------|-----|------------------|-----------------|----------------|----------------------------|

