## 5. STUDY PLAN

### 5.1. DURATION OF STUDY (WHOLE POPULATION)

The total duration of the study will be approximately 84 months, including about 72 months of active enrollment.

Planned start date (first patient on study): February 2018.

The planned study termination (clinical cutoff) will be 12 months after the last patient is included.

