## **5.2. DEFINITIONS OF DURATION OF STUDY AND TREATMENT (PER PATIENT)**

Patients will receive study treatment as long as it is considered to be in their best interest. Patients will be evaluated at scheduled visits in up to five study periods:

- **Pre-treatment (PRE TT):** from signature of informed consent to the first administration of study drugs.
- **Treatment (TT):** from the first administration of study drugs to treatment discontinuation
- **Safety follow-up (SFUP):** after treatment discontinuation, safety follow-up must be performed 30 days after the last treatment administration (toxicity assessment).
- **Extended safety follow-up (ESFUP):** given the potential risk for delayed immune-related toxicities, extended safety follow-up must be performed up to 90 days after the last dose of avelumab administration (ie. 60 days after SFUP). This visit may be performed either via a site visit or via a telephone call with subsequent site visit requested in case any concerns noted during the telephone call
- **Follow-up (FUP):**

After safety follow-up visit, patients who discontinue treatment without progression will be followed **every 12 weeks until:**

1. Disease progression,
2. Initiation of other antitumor therapy,
3. Death, or
4. The date of study termination, whichever occurs first.

After documented progression or start of a new antitumor therapy, patients will be **followed every 6 months until:**

1. Death, or
2. The date of study termination, whichever occurs first.

Patients will be considered to be **on-study** from the signature of the informed consent to the end of follow-up period.

Patients will be considered to be **on-treatment** for the duration of their treatment until 90 days after the last treatment administration, except if the patient starts a new antitumor therapy before this period. Patients may withdraw their consent at any time; no further study activities will be conducted on them.

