### **9.2.2.Secondary endpoints**

- Best overall response is defined as the best response across all time points (RECIST v1.1). Following RECIST v1.1 recommendations:
  - The best overall response is determined once all the data for the patient is known.
  - The best overall response will be classified as confirmed complete response (CR), unconfirmed complete response (CRu), confirmed partial response (PR), unconfirmed partial response (PRu), stable disease or progressive disease, as per RECIST v1.1 criteria.
  - As per RECIST v1.1 criteria, to be considered as “confirmed”, complete and partial responses will have to be confirmed at least 4 weeks later to ensure responses identified are not the result of measurement errors.
- Objective response rate at 6 months (6-month ORR) is defined as the proportion of patients with objective response (confirmed or unconfirmed) at 6 months.
- Progression-free status is defined as complete response (confirmed or unconfirmed), partial response (confirmed or unconfirmed) or stable disease more than 24 weeks as defined as per RECIST v1.1 criteria (appendix 3). 6-month progression-free rate (6-month PFR) is defined as the proportion of patients with progression-free status at 6 months. 4-month progression-free rate (4-month PFR) is defined as the proportion of patients with progression-free status at 4 months.
- Growth modulation index (GMI): GMI is defined for each patient as the ratio of its PFS on Regorafenib + Avelumab treatment to its PFS on the previous line of therapy. This method accounts for inter-patient variability, the patient serving as his/her own control and implies by the natural history of the disease that the PFS tends to become shorter in successive lines of therapy. It is thought that an anti-cancer agent should be considered effective if the GMI is greater than 1.3
- Progression-free survival (PFS) is defined as the time from study treatment initiation to the first occurrence of disease progression or death (of any cause), whichever occurs first. 1-year PFS rate and median PFS will be reported.

- Overall Survival (OS) is defined as the time from study treatment initiation to death (of any cause). 1-year OS rate and median OS will be reported.
- Safety profile of the association Regorafenib + Avelumab: Toxicity will be graded using the common toxicity criteria from the NCI v5.0.
- Pharmacodynamic activity:
  - archived tumor tissue will be collected for assessment of the tumor microenvironment.

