#### **10.3.2. Endpoint analyses**

##### 10.3.2.1. PHASE I TRIAL (DOSE ESCALATION PART)

- All analyses will be descriptive; no p-values will be calculated.
- Primary endpoint will be analyzed on the population assessable for safety of the phase I trial (escalation part).
- Toxicity observed at each dose level, graded according to the Common Terminology Criteria for Adverse Events v5.0 from the NCI, will be recorded in terms of event type, severity, dates of beginning and end, reversibility and evolution. Data will be gathered in tables summarizing toxicities and side effects for each dose level and cycle.
- DLT will be described in terms of number and incidence rates at each dose level. The number and percentage of patients who will have developed a DLT in each dose level will also be reported.
- Data analyses will be provided by dose groups and for all study patients, combined wherever appropriate.
- Categorical endpoints: best overall response, ORR under treatment and at 6 months, 6-month ORR and 6-month PFR, will be reported in terms of counts by dose level.
- Continuous endpoints, e.g. GMI, will be reported in terms of summary statistics that will include number of patients, median, minimum, and maximum, and additional percentiles if appropriate.
- Survival endpoints (PFS and OS) will be analyzed using the Kaplan-Meier method. The median survival rates will be reported with a 95% confidence interval. Median follow-up will be calculated using the reverse Kaplan-Meier method.
- Missing data will not be imputed.

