- Quantitative variables will be described using mean and standard deviations if the normality assumption is satisfied, else other descriptive statistics (median, range, quartiles) will be reported.
- Qualitative variables will be described using frequency, percentage and 95% confidence interval (binomial law).
- Survival endpoints will be analysed using the Kaplan-Meier method. The median survival rates will be reported with a 95% confidence interval. Median follow-up will be calculated using the reverse Kaplan-Meier method.

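### The protocol summarises the growth modulation index with uncensored statistics although its numerator, on-study PFS, is right-censored, so the summary sits at or below the truth by an amount set by the censoring; low priority

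*Protocol*

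**What the plan says.** Protocol section 9.2.2 (and 9.1.2 for phase I) defines GMI for each patient as "the ratio of its PFS on Regorafenib + Avelumab treatment to its PFS on the previous line of therapy". Both sections add, as background, that an agent is thought to be effective when GMI exceeds 1.3.

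Section 10.3.2.1 fixes the summary: "Continuous endpoints, e.g. GMI, will be reported in terms of summary statistics that will include number of patients, median, minimum, and maximum", with further percentiles if appropriate. The next bullet treats the numerator differently: "Survival endpoints (PFS and OS) will be analyzed using the Kaplan-Meier method".

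For phase II, the statistical analyses part of the synopsis says: "Same statistical methods as for the phase I trial". Section 10.3.2.2 does not name GMI but keeps the same split. "Quantitative variables will be described using mean and standard deviations if the normality assumption is satisfied", otherwise by median, range and quartiles; and "Survival endpoints will be analysed using the Kaplan-Meier method".

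On follow-up, section 5.2 ends the 12-weekly follow-up of patients who stop treatment without progression at progression, death, study termination or "Initiation of other antitumor therapy". Section 5.7 stops all procedures after withdrawal of consent. Section 5.1 states: "The planned study termination (clinical cutoff) will be 12 months after the last patient is included".

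**The concern.** The numerator of GMI is a time that can be right-censored, and the protocol recognises this when it sends PFS to Kaplan-Meier. The ratio built on that time is nevertheless placed with ordinary continuous variables. A plain median and range can be computed only by taking the censored time as if it were the PFS, or by leaving the patient out. Long PFS times are the ones most exposed to censoring, so either route tends to lose the best results.

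What is at stake is how a descriptive secondary endpoint reads. The cohorts are single-arm, and GMI is the one endpoint presented as using the patient as his or her own control. Readers will naturally compare its median with the 1.3 mentioned in the endpoint definition.

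**Working it through.** The protocol states no expected GMI, sample size or power for it, so there is no figure to reproduce. The check covers direction first, then size.

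**Direction.** Let T be true on-study PFS, C the censoring time and P the PFS on the previous line. P is largely observed, because section 4.1 requires documented progression before entry. The raw index is min(T, C)/P, and min(T, C) ≤ T, so raw GMI ≤ true GMI for every patient. Every order statistic (median, maximum, percentiles) is then at or below its uncensored value.

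**Inputs for size.**
- From the document: 6-month progression-free rates of 20% and 40% (cohort H, section 10.1.3), used only to scale PFS. With exponential PFS the hazard is λ = −ln(rate)/6 and the median is ln 2/λ, which gives 2.58 and 4.54 months. The proportion beyond 12 months is rate²: 0.20² = 4% and 0.40² = 16%.
- Assumed: exponential previous-line PFS, correlation 0 or 0.5 between the two PFS times (Gaussian copula), true median GMI 1.30, and the censoring patterns below.

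**Closed form for random censoring.** Take independent PFS times and exponential censoring that removes a share p. Then min(T, C) is exponential with hazard λ/(1 − p), so the raw median is 1.30 × (1 − p):
- 10%: 1.30 × 0.90 = 1.17
- 20%: 1.30 × 0.80 = 1.04
- 40%: 1.30 × 0.60 = 0.78

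In this case, PFS among patients with an observed event has the same distribution, so dropping censored patients gives the same medians.

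**Simulation** (400,000 patients per scenario; true median 1.30; ranges span the scenarios in each row):

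| Censoring | Share censored | Median, censored times kept | Median, censored patients dropped | Median, Kaplan-Meier on the ratio |
|---|---|---|---|---|
| Administrative, at 12 months or later | 1-4% | 1.28-1.30 | 1.20-1.29 | 1.30-1.32 |
| Administrative, all at 12 months, 6-month rate 40% | 16% | 1.20-1.24 | 0.96-1.10 | 1.35-1.38 |
| Random | 20% | 1.04-1.06 | 1.04-1.16 | 1.39-1.44 |
| Random | 40% | 0.78-0.81 | 0.78-1.00 | 1.55-1.71 |

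The 20% and 40% rows agree with the closed form. Upper percentiles fall too: with 20% random censoring and uncorrelated times, the 90th percentile drops from 11.7 to 9.4.

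The last column matters for the repair. Censoring on the ratio scale happens at C/P, which depends on P just as the ratio T/P does. The independence that Kaplan-Meier needs therefore fails, and the estimate is too high.

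**The case against.** - **Nothing depends on GMI.** Section 10.3.2 makes the analyses descriptive without p-values, and no stopping or success rule in sections 10.1.2 to 10.1.10 uses GMI. A reader might infer that 1.3 works as an efficacy threshold whose verdict would be distorted. The text does not support that: 1.3 is background in the endpoint definition. Nor is a share of patients above 1.3 planned, so no planned share is understated. This stands and sets the priority.
- **This is SAP detail.** Section 10.3 promises SAPs before the first analyses, and the list in 10.3.2.1 is not closed. That would answer a protocol that was silent. This one names GMI, gives it the statistics of an uncensored variable, and sends its numerator to Kaplan-Meier in the next bullet. A SAP that handled censoring properly would have to depart from that classification.
- **The anchor is phase I, with 6-12 patients.** True, and section 10.3.2.2 does not name GMI. The synopsis nevertheless carries the methods over, and 10.3.2.2 offers only the same plain summaries for quantitative variables.
- **Censoring may be light.** Patients off treatment are followed to progression, and section 5.1.2 keeps the study open until all have progressed or stopped study medication. A reader might infer that a large downward bias is certain. It is not: the protocol states neither a censoring rate nor its PFS censoring rule, and light, late censoring barely moves the median if censored times are kept.
- **Kaplan-Meier on the ratio is biased too.** Correct. It overshoots, and at 16% censored its error (+0.05 to +0.08) is close in size to that of the raw median (−0.06 to −0.10). It cannot be offered as a clean cure.

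**Conclusion.** The point holds with a limited claim. The protocol prescribes uncensored summary statistics for a right-censored quantity. With censored times kept, the result is at or below the truth by construction. With censored patients dropped, the median was lower in every simulated scenario.

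The error is negligible with 1-4% late administrative censoring if censored times are kept. It becomes material at roughly 10% or more early censoring: a true median of 1.30 reads as about 1.17 at 10% and 1.05 at 20%. These sizes rest on exponential PFS and assumed censoring shares; the direction with censored times kept does not. Because GMI is descriptive, secondary and outside every decision rule, the priority is low and the cohorts' primary conclusions are unaffected.

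**What to change.** In sections 10.3.2.1 and 10.3.2.2, and in the matching synopsis lines:
- Take GMI out of the plain continuous endpoints and define it as right-censored whenever on-study PFS is censored.
- Report the number of censored GMIs in each cohort or dose group.
- Estimate the median with a 95% CI by a method for censored paired times. Alternatively use Kaplan-Meier on the ratio, stating that censoring on that scale depends on previous-line PFS and biases the estimate upward.
- If a share above 1.3 is reported, give lower and upper bounds, counting GMIs censored at or below 1.3 first as failures and then as successes. A GMI censored above 1.3 is a known success.

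The cost is a few sentences and slightly more analysis work, with no new data collection. If Kaplan-Meier is chosen, a residual upward bias remains, and under heavy censoring it is not small.

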##### 10.3.2.2. PHASE II TRIALS

- All analyses will be descriptive; no p-values will be calculated.
- Analyses will be conducted independently for each phase II trial.
- Analysis of the primary efficacy endpoint will be analysed based on the eligible population assessable for efficacy (see chapter 10.2 for definition):
  - Each patient will be assigned one of the following categories:
    - Confirmed complete response (CR)
    - Unconfirmed complete response (CRu)
    - Confirmed Partial response (PR)
    - Unconfirmed Partial response (PRu)
    - Stable disease
    - Progression (Clinical PD and radiological PD will be reported separately)

- Inevaluable for response
- Depending on the cohort, the rate of objective response (ORR: CR, CRu, PR, PRu) under treatment or the progression-free rate (PFR: CR, CRu, PR, PRu, SD) will be reported:
  - All eligible and assessable patients (section 10.2) will be included in the denominator for the calculation of the ORR/PFR.
  - The 95% two-sided confidence limits will be provided for the ORR/PFR (binomial law).
  - First endpoint conclusions will be based on the ORR/PFR for all eligible and assessable patients (section 10.2) after centralized radiological review of the data.
- As regards to the other efficacy endpoints, the analyses will be carried out in the eligible and assessable population:
  - Each patient will be assigned one of the following categories:
    - Confirmed complete response (CR)
    - Unconfirmed complete response (CRu)
    - Confirmed Partial response (PR)
    - Unconfirmed Partial response (PRu)
    - Stable disease
    - Progression
    - Inevaluable for response
  - The rate of best overall response will be calculated as the number of patients alive with the best response (recorded from the start of the treatment) divided by the number of patients eligible and assessable (section 10.2).
  - The 6-month progression-free rate will be calculated as the number of patients remaining alive and progression-free at 6 months from the start of the treatment divided by the number of patients eligible and assessable (section 10.2).
  - The 6-month objective response rate will be calculated as the number of patients alive with complete or partial response at 6 months divided by the number of patients eligible and assessable (section 10.2).
  - The 95% two-sided confidence limits will be provided for the calculated rates (binomial law)
- The safety analysis will be performed on the safety population.
- Quantitative variables will be described using mean and standard deviations if the normality assumption is satisfied, else other descriptive statistics (median, range, quartiles) will be reported.
- Qualitative variables will be described using frequency, percentage and 95% confidence interval (binomial law).
- Survival endpoints will be analysed using the Kaplan-Meier method. The median survival rates will be reported with a 95% confidence interval. Median follow-up will be calculated using the reverse Kaplan-Meier method.

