| Number of patients                      | Phase I (escalation part): 6-12 patients
Phase II (expansion cohorts): 735 patients                                                                                                                                                                                                                                                                                                                                                                                                                                                                                                                                                                                                                                                                                                                                                                                                                                                                                                                                                                                                                                                                                                                                                                                                                                                                                                                                                                                                                                                                                                                                                                                          |

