**For phases II trials and all cohorts, except cohort A':**

| Regimen Description |                                               |       |                                                                                |                              |
|---------------------|-----------------------------------------------|-------|--------------------------------------------------------------------------------|------------------------------|
| Agent               | Dose                                          | Route | Schedule                                                                       | Cycle length                 |
| Avelumab            | 10 mg/kg                                      | I.V.  | Every 2 weeks
(start on Cycle 1 Day 15.
D1 and D15 of subsequent cycles) | 28 days
(4 weeks) |
| Regorafenib         | Dose as defined in the phase I trial: 160 mg. | Oral  | Continuous, once daily
Day 1-Day 21                                         |                              |

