#### 10.1.2. Phase II trials: Cohorts A, B, C, D, E, F, G

Independently for each of these phase II trials, a Bayesian approach will be used following an adaptive trial design, allowing for smaller and more informative trials, specifically tied to decision making within a drug development program. This process allows updating knowledge gradually rather than restricting revisions in a trial design with fixed sample sizes.

In each phase II trial:

- A maximum sample size of 50 patients will be included.
- The analysis of the primary endpoint (ORR under treatment for cohorts A as well as C to G; 6-month PFR for cohort B) will be carried out sequentially, with interim analyses planned after 16-week follow-up of the first 10 patients and then every 5 patients. Inclusions will not be suspended between interim analyses, except in case of an important accrual rate in a given given trial (2 patients/center/months during at least 3 months).
- ORR (for cohorts A as well as C to G) or 6-month PFR (for cohort B) will be estimated in the eligible population assessable for efficacy (section 10.2.2). The probability of success (ORR under treatment or 6-month PFR) will be estimated from a beta-binomial model (Zohar et al., 2008). Initial parameters of the model will be pre-specified (the prior distribution represents the knowledge of the non-progression probability prior to observing the data). Successive results observed will then be used to update and refine the distribution, generating the so-called posterior distribution.
- In the absence of a strong idea about the response rates to be observed, a non-informative prior distribution (beta (1,1)) will be considered.
- Maximal response probability thresholds (based on the investigator' opinions) and minimal response probability threshold have been defined as follows:
  - Cohort A/E:  $p_0=5\%$  versus  $p_1=20\%$
  - Cohorts B/C/D/F:  $p_0=20\%$  versus  $p_1=40\%$
  - Cohorts G:  $p_0=10\%$  versus  $p_1=25\%$
- At each update of the distribution (interim analysis), a stopping rule for inefficacy will recommend stopping the trial if there is a high predictive probability ( $\geq 80\%$ ) that the ORR (for cohorts A as well as C to G) or 6-month PFR (for cohort B) is lower or equal to the minimal response probability threshold  $p_0$  defined for the cohort (Strata A and E:  $p_0=5\%$ ; Strata B/C/D/F:  $p_0=20\%$ ; Stratum G:  $p_0=10\%$ ).

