#### **10.2.2. Phase II trials**

Independently for each phase II trial:

- Eligible population: All patients included without major violation of eligibility criteria.
- Eligible population assessable for efficacy: All patients eligible and for whom the following conditions are satisfied:
  - Received at least one complete cycle over the first two cycles (i.e. both Regorafenib and Avelumab received fully over at least one cycle) or two incomplete treatment cycles (i.e. at least Regorafenib or at least Avelumab partially administered over each of the first two cycles),
  - At least one disease measurement recorded not less than eight weeks after treatment onset.
- The following patients will also be included in the population assessable for efficacy; they will be considered as "inevaluable for response" for the primary endpoint as per RECIST v1.1 criteria (i.e. objective response under treatment) and not be replaced in the primary efficacy analysis:
  - Any eligible patients who received at least one treatment cycle or two incomplete treatment cycles and experience disease progression or die due to disease progression prior to response evaluation (will be considered as "inevaluable for response" due to early progression or death related to progression).
- Safety population: all patients who initiated treatment (Regorafenib or Avelumab).

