#### 10.3.2.3. PHASE II TRIALS – INTERIM SAFETY ANALYSIS

- An interim safety analysis will be performed based on the first ten patients included in (any of) the phase II trials.
- This analysis will be performed once data over the first cycle of treatment are available for the first 10 patients.
- Pooled data will be presented.
- Baseline patients' characteristics, treatment, and safety data (SAE and AE) will be presented over the first cycle of treatment.

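### Final phase II safety is planned cohort by cohort although 16 of 17 cohorts share one regimen; a supplementary pooled safety table would give far more precise rates for uncommon toxicities

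*Protocol*

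**What the plan says.** Section 10.3.2.2 sets the unit of analysis: "Analyses will be conducted independently for each phase II trial". Further down the same list it adds: "The safety analysis will be performed on the safety population". Nothing there exempts safety from the first rule. Section 10.2.2 defines the set as "Safety population: all patients who initiated treatment (Regorafenib or Avelumab", under a lead-in that applies each definition separately to every phase II trial. Section 2.2.2 places the safety objective under a similar lead-in. No pooled final safety analysis is named.

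Two other places point towards pooling:

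- **Regimen.** Section 7.3 gives one regimen table for all phase II cohorts except A'. Avelumab is 10 mg/kg every two weeks, and the regorafenib entry reads "Dose as defined in the phase I trial: 160 mg". Cohort A' has its own table, at 80 mg. The synopsis treatment schedule makes the same split.
- **Interim safety.** Section 10.3.2.3 takes the first ten patients from any of the phase II trials, over cycle 1, and says: "Pooled data will be presented".

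**The concern.** Independence by cohort is needed for efficacy, because each cohort has its own endpoint, thresholds and decision rule. Safety has no such rule in phase II. The toxicity of the combination is a shared question for the 16 cohorts on one regimen. The protocol accepts this at ten patients and then returns to separate cohorts when several hundred have been treated.

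The events for which the denominator matters most are ones the protocol singles out. Appendix 8 has management tables for pneumonitis and myocarditis, and section 11.4 makes potential drug-induced liver injury an event of special interest. If such events are uncommon, most cohort tables will show none or one, with an interval too wide to be useful.

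**Working it through.** **Inputs.** The synopsis gives the total: "Phase II (expansion cohorts): 735 patients". Planned inclusions by cohort come from the synopsis and section 10.1:

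- A to G: at most 50 each. Section 10.1.2 says "A maximum sample size of 50 patients will be included".
- H 47, I 32, A' 47.
- J, L and N: 31 each. K and P: 44 each. M and O: 39 each.

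**Reproducing the plan's total.** 7×50 + 47 + 32 + 47 + 3×31 + 2×44 + 2×39 = 350 + 126 + 93 + 88 + 78 = 735, an exact match. Removing A' leaves 735 − 47 = 688 patients in 16 cohorts on the common regimen.

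**Safety denominator per cohort.** Safety counts every treated patient, so the planned range is 31 to 50. The 28 quoted for J, L and N is the efficacy-assessable number. Cohorts A to G can be smaller still, since they are examined "with interim analyses planned after 16-week follow-up of the first 10 patients and then every 5 patients" and may stop at any of those analyses.

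**Early-stopping case (illustrative).** If A to G all stop at 10, H and I stop at 13, and J to P complete, the pooled number is 70 + 26 + 259 = 355.

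**Formulae.** For a true rate p, the chance of at least one case in n patients is 1 − (1 − p)^n. With no events, the two-sided 95% upper limit (exact binomial, in line with the binomial intervals of section 10.3.2.2) is 1 − 0.025^(1/n). The documents give no rate for uncommon toxicities, so 0.5%, 1% and 2% are assumptions.

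| n | Chance, 0.5% | Chance, 1% | Chance, 2% | Upper limit, no events |
|---|---|---|---|---|
| 10 (A to G, earliest stop) | 4.9% | 9.6% | 18.3% | 30.8% |
| 31 (smallest planned cohort) | 14.4% | 26.8% | 46.5% | 11.2% |
| 50 (largest planned cohort) | 22.2% | 39.5% | 63.6% | 7.1% |
| 355 (pooled, early stopping) | 83.1% | 97.2% | 99.9% | 1.03% |
| 688 (pooled, full accrual) | 96.8% | 99.9% | >99.9% | 0.53% |

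Worked lines for 1%: 1 − 0.99^31 = 0.268; 1 − 0.99^50 = 0.395; 1 − 0.99^688 = 0.999. For no events: 1 − 0.025^(1/31) = 0.112; 1 − 0.025^(1/688) = 0.0053.

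**When events do occur.** One event gives an exact 95% interval of 0.1% to 16.7% in 31 patients and 0.05% to 10.6% in 50. Pooled, 7 of 688 (1%) gives 0.4% to 2.1%, and 14 of 688 (2%) gives 1.1% to 3.4%.

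**What pooling hides.** Cohorts A to G total 350 and exclude prior checkpoint inhibitors (section 4.2, criterion 2). The other cohorts on the common regimen total 688 − 350 = 338. If the true rates were 1% and 3% in these two groups (assumed for illustration), the pooled rate would be (350×0.01 + 338×0.03)/688 = 2.0%, which describes neither.

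**The case against.** **The plan matches its objective.** Section 2.2.2 asks for safety trial by trial, and estimating uncommon toxicities is not a stated aim. This stands: the plan does not contradict itself, and the proposal is an addition.

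**A statistical analysis plan could add the table.** Section 10.3 commits to one before the first phase II analysis, and a supplementary table can be set there. But the protocol is not silent. Three sections make the cohort the unit for safety, so a pooled analysis would sit awkwardly with that wording.

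**The protocol may already allow pooling.** The synopsis says phase II uses the phase I methods, and section 10.3.2.1 lets phase I data be combined where suitable. That route is too indirect to count as a plan, and the synopsis repeats the independence rule for phase II.

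**Stronger readings.** A reader might infer that rare serious toxicities would go undetected. The documents do not support this. Section 11.3 sends serious events from every cohort to one Vigilance Unit, which under section 11.7 assesses each for relationship and expectedness; the Steering Committee follows benefit and risk (section 12.1.1). What is missing is a rate with a usable denominator. Nor is it right that the rates cannot be estimated: each cohort gives an estimate, but a very imprecise one. A reader might also expect the events to be scattered over 17 separate reports, but nothing in the protocol provides for these.

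**One regimen is not one population.** This stands. A to G exclude prior checkpoint inhibitors. H and J require at least four months of PD-(L)1 treatment, as does L with an exception for CPS below 10. K, M, N, O and P allow either history. Cohort D includes hepatocellular carcinoma, which matters for hepatic events. Pooling is therefore not free of cost, and the pooled column needs strata beside it.

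**Conclusion.** The point holds as a recommended, inexpensive improvement to a stated analysis choice. It does not show an error in a decision rule. Final safety is fixed by cohort, 16 of 17 cohorts share a regimen, and the protocol already pools safety at ten patients. At planned size, pooling narrows the zero-event two-sided 95% upper limit from between 11.2% and 7.1% to 0.53%. For a 1% event it raises the chance of seeing a case from between 26.8% and 39.5% to 99.9%. Most of the gain survives heavy early stopping (1.03% and 97.2% at 355 patients).

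This rests on the assumed event rates, on planned accrual for the 688, and on reading the pooled figure as an average over differing populations. Phase II analyses are descriptive, so no error rate or efficacy decision is affected.

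**What to change.** Keep the safety tables by cohort. Add to section 10.3.2.2, as a stated exception to the independence rule, a supplementary descriptive safety analysis pooled over all patients treated at the recommended phase II dose (every cohort except A'). It should:

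- show A' (80 mg) separately alongside;
- show rates by cohort and by prior checkpoint-inhibitor exposure;
- identify the hepatocellular carcinoma patients of cohort D for hepatic events.

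Align sections 2.2.2 and 10.2.2, which otherwise would still tie safety to the single trial, and the independence rule repeated in the synopsis.

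The cost is one extra set of tables from data already collected, with no added patients. The downside is a pooled rate that mixes populations and must be read beside the strata.
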